## Abstract

**Introduction:**

Diagnosis of infantile thiamine deficiency disorders (TDD) is challenging due to the non-specific, highly variable clinical presentation, often leading to misdiagnosis. Our primary objective is to develop a case definition for thiamine responsive disorders (TRD) to determine among hospitalised infants and young children, which clinical features and risk factors identify those who respond positively to thiamine administration.

**Methods and analysis:**

This prospective study will enrol 662 children (aged 21 days to <18 months) seeking treatment for TDD symptoms. Children will be treated with intravenous or intramuscular thiamine (100 mg daily for a minimum of 3 days) alongside other interventions deemed appropriate. Baseline assessments, prior to thiamine administration, include a physical examination, echocardiogram and venous blood draw for the determination of thiamine biomarkers. Follow-up assessments include physical examinations (after 4, 8, 12, 24, 36, 48 and 72 hours), echocardiogram (after 24 and 48 hours) and one cranial ultrasound. During the hospital stay, maternal blood and breast-milk samples and diet, health, anthropometric and socio-demographic information will be collected for mother–child pairs. Using these data, a panel of expert paediatricians will determine TRD status for use as the dependent variable in logistic regression models. Models identifying predictors of TRD will be developed and validated for various scenarios. Clinical prediction model performance will be quantified by empirical area under the receiver operating characteristic curve, using resampling cross validation. A frequency-matched community-based cohort of mother–child pairs (n=265) will serve as comparison group for evaluation of potential risk factors for TRD.

**Ethics and dissemination:**

Ethical approval has been obtained from The National Ethics Committee for Health Research, Ministry of Health, Lao PDR and the Institutional Review Board of the University of California Davis. The results will be disseminated via scientific articles, presentations and workshops with representatives of the Ministry of Health.

**Trial registration number:**

NCT03626337.

Strengths and limitations of this studyA standardised case definition for thiamine responsive disorder (TRD) will be proposed, through understanding of the interplay between clinical presentation, response to therapeutic thiamine administration and biochemical analyses, which will help more accurately diagnose TRD among infants and young children.The broad spectrum of eligibility criteria will ensure inclusion of hospitalised infants and young children who may have milder, underlying thiamine deficiency and may respond clinically and benefit from thiamine administration, as well as those with suspected beriberi.Associations between TRD and biomarkers of thiamine status will help establish deficiency cut-off thresholds for thiamine diphosphate and erythrocyte transketolase activity coefficient that are relevant to a population with thiamine deficiency.Due to ethical considerations, this study does not include a placebo control group and will rely on a community comparison group to cross-check risk factors identified in the hospitalised cohort to a healthier population.In addition to the thiamine administration, hospitalised children will continue to receive routine care, such as antibiotics and other medications for concurrent illnesses that may affect the children’s recovery, making the clear distinction between TRD cases and non-responders more challenging.

## Introduction

Thiamine (vitamin B_1_) is an essential micronutrient, required as a cofactor for several enzymes involved in carbohydrate metabolism and energy production. Thiamine deficiency has been described in several low-income and middle-income countries and remains a public health concern in many countries of Southeast Asia,^1 2^ including Lao People’s Democratic Republic (Lao PDR).^3–5^ Diets that lack in dietary diversity and rely too heavily on low-thiamine staple crops (such as polished white rice), food preparation practices (repetitive washing and soaking rice for many hours) and traditional postpartum restrictive diets, all place lactating women at high risk of thiamine deficiency in Lao PDR.^6–8^ Breast-milk thiamine concentrations and infant thiamine status are strongly dependent on maternal thiamine intake and status, and maternal thiamine deficiency rapidly results in low breast-milk thiamine concentrations.^9^ Infants are therefore especially vulnerable to thiamine deficiency in the first months of life, and exclusively breastfed infants of thiamine-deficient mothers are at the highest risk. According to the WHO, infantile thiamine deficiency is the only serious form of malnutrition that occurs in adequately breastfed infants and only when the mother herself is thiamine-deficient.^10^

Thiamine deficiency presents as a broad spectrum of non-specific clinical abnormalities, referred to as thiamine deficiency disorders (TDD), of which the classic forms of beriberi in adults and children are best known, although even classic beriberi often goes unrecognised.^11^ TDD can be characterised to some degree by age and features of clinical presentation.^2^ Infantile TDD commonly occurs between 1 and 9 months of age, with non-specific early signs such as refusal to breast feed, vomiting and irritability (1–3 months of age), which can progress to oedema, respiratory distress, heart failure and death if not rapidly treated. During later infancy, the cry may sound hoarse or change to a soundless cry (4–6 months of age) and neurological symptoms may present, including nystagmus, convulsions and unconsciousness (7–9 months of age). Infants with encephalitic beriberi were found to have abnormal cranial ultrasonography, with normalisation within 8 weeks of thiamine administration.^12^ In the second year of life and later in childhood, TDD more typically presents with a broad range of neurological symptoms, such as anorexia, irritability, agitation, muscle pain, reduced deep tendon reflexes, ataxia, paralysis and altered levels of consciousness.^11 13–15^ Due to uncertainties regarding the diagnostic criteria and overlapping symptoms with other conditions, TDD may frequently be misdiagnosed as bronchiolitis, pneumonia, typhoid fever, sepsis, meningitis or encephalitis, and the underlying thiamine deficiency may remain untreated.^1 2 11^ Cases of TDD are often suspected rather than confirmed, and a final diagnosis is usually based on a positive response to intramuscular or intravenous thiamine administration.

Diagnosis of TDD is further complicated by the fact that several studies have found little association between biomarkers of thiamine status and TDD-like symptoms.^16–18^ It has been suggested that low thiamine status alone cannot reliably discriminate between symptomatic and asymptomatic infants, and infectious co-pathologies and other physiological stressors may precipitate the onset of TDD.^17^ Conversely, low thiamine status appears to increase vulnerability to disease, as indicated by the observation that hospitalised infants with low thiamine status, but no clinical signs of beriberi, showed higher mortality rates in a region of Lao PDR.^4^

Thiamine status can be determined by assessing thiamine metabolites in blood or urine. The most widely used biochemical indicator of thiamine status is the activity of the thiamine-dependent transketolase enzyme in erythrocytes (ETK), which reflects the biological functionality of the vitamin and is sensitive to marginal thiamine deficiency.^19^ Thiamine diphosphate (ThDP) concentration in whole blood or erythrocytes is also a useful indicator as ThDP is the biologically active vitamer and is reflective of body stores. There are however many challenges to assessing biomarkers of thiamine status, especially in resource-limited settings, including cost, the required cold chain and limited availability of laboratories able to analyse biological specimens. Hence, thiamine biomarkers are not routinely assessed and a rapid positive response to therapeutic thiamine is considered confirmation of a deficient status. Furthermore, there are currently no universally agreed on adequacy or deficiency cut-off thresholds for erythrocyte or whole blood ThDP or ETK activity coefficient (ETKac), which have largely been studied in thiamine adequate adults in high-income countries. Consequently, a wide range of cut-offs has been used.^1^ Limited data derived from two studies in European adults at risk of thiamine deficiency from either chronic alcoholism or from an acute or chronic medical condition are available on associations between ETKac and ThDP.^20 21^ These studies suggest that elevated ETKac (≥25%) occurs when ThDP concentrations are below 280 mg/g haemoglobin. However, it is not clear if similar results would be apparent in other populations. Thus, there is a need to develop clinically meaningful cut-off thresholds for biomarkers indicative of thiamine deficiency in other at-risk populations, especially infants and young children in countries where thiamine intake is inadequate and exclusive breast feeding is prevalent.

In summary, owing to the wide variability in clinical presentation, a barrier for reliable diagnosis and targeted treatment of TDD is the lack of a clear clinical case definition with broad consensus. There is a need to understand the interaction between thiamine status, exposure to risk factors (including infections) and onset of clinical symptoms in areas where thiamine deficiency is prevalent. Thus, this study aims to develop a standardised case definition for thiamine responsive disorders (TRD), based on a combination of presenting clinical features most predictive of responding to therapeutic thiamine doses, alongside assessment of biochemical indicators of thiamine status and potential risk factors, in infants and young children aged 21 days to <18 months in Lao PDR.

## Objectives of study

The primary objective of this study is the development of a case definition for TRD among infants and young children with symptoms consistent with TDD, with the case definition based on those clinical symptoms and other predictors that we find are better able to distinguish those who respond positively to thiamine administration from those who do not respond. As diagnostic tools available to treating physicians may differ by setting, we will repeat analyses after excluding from the set of candidate predictors those that are derived from assessments only available in higher-resource settings, such as laboratory biomarkers and ultrasonography.

A secondary objective is to fill the knowledge gap surrounding biomarkers of thiamine status in at-risk populations. Biomarker cut-offs for TRD will be developed in the hospital cohort and distributions will be characterised in both the hospital and community cohorts. The performance of our proposed cut-off will be compared with the performance of existing literature cut-offs.

Additionally, all identified predictors and biomarker cut-offs will be compared across the community cohort, non-TRD hospital cohort and TRD hospital cohort to assess the prevalence of risk factors among apparently healthy infants and young children and assess the usefulness of the TRD case definition in various settings.

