For our secondary research questions concerned with describing TRD risk factors across a community comparison cohort and our two hospital cohorts, we plan to enrol 212 region, age and sex frequency-matched children (increased to 265 after adding the inflation factor of 1.25 for potential blood collection failure). Given a hospital cohort split between TRD groups of sizes 60–106 and 424–470, this would provide at least 80% power to detect an independent variable for which a 1 SD increase is associated with an adjusted OR of 1.6, under two-sided testing (of the null hypothesis that the adjusted OR is 1) with alpha=5%, even when other covariates in the models account for as much as 20% of the variation in that independent variable. For a binary risk factor present in 20% of children, the detectable adjusted OR under the stated assumptions would be 2.45. Hence, we anticipate having adequate statistical power to detect risk factors associated with moderate to strong incremental discriminative capacity.

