#### Statistical analysis

Prior to performing statistical analyses, detailed statistical analysis plans will be developed and published online.^39^

Our primary model development objective will seek to achieve case definition models that provide high discrimination capacity and acceptable calibration in external samples, using principled approaches to guard against overfitting biases. It is likely that there will be ambiguity in TRD determination due to a range of potential thresholds for what is considered ‘recovery‘. Consequently, sensitivity analyses may be repeated with different variations of TRD definitions. These definitions will be defined prior to analysis by expert paediatricians. We will follow a three-staged approach to identifying candidate risk factors and selecting among them. In the first stage, investigators will specify risk predictors that could be reliably and validly measured early in the hospitalisation in limited-resource settings and which are plausibly associated with TRD status. In the second stage, we will develop and validate logistic regression models, using TRD status as the dependent variable and using elastic net regression and related approaches to principled variable selection. In the third stage, we will repeat the analysis incorporating more sophisticated diagnostic assessments, such as biomarkers and ultrasound, which are available in higher resource settings. Finally, after each clinical prediction model is developed, we will use resampling methods with 10-fold cross validation to estimate model performance in terms of discriminative capacity, as measured by empirical AUROC, internally and externally.

Our secondary objective of establishing biomarker cut-offs for TRD will follow a similar receiver operating characteristic curve-based approach, except with specific biomarker concentrations as the principle predictor. A weighted evaluation of each cut-offs sensitivity and specificity will be used in a 10-fold cross-validation framework to select the optimal cut-off.^40^

The comparison of predictors, biomarkers and risk factors across the community cohort, non-TRD hospital cohort and TRD hospital cohort will be contextual and dependent on the type of variable considered. Analyses will be primarily descriptive, focused on substantive differences between cohorts, accompanied by visualisations and distribution-appropriate statistical testing.

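### Ordinary tests of model-selected predictors in the same TRD and non-TRD children used to select them will not have their nominal error rate

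*Protocol article*

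**What the plan says.** The primary objective (Objectives of study) bases the case definition on presenting signs together with "other predictors that we find are better able to distinguish those who respond positively to thiamine administration from those who do not respond". The Statistical analysis section gives the method: logistic models "using TRD status as the dependent variable and using elastic net regression and related approaches to principled variable selection". For the secondary objective, "Biomarker cut-offs for TRD will be developed in the hospital cohort and distributions will be characterised in both the hospital and community cohorts".

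The same objectives section then says that "all identified predictors and biomarker cut-offs will be compared across the community cohort, non-TRD hospital cohort and TRD hospital cohort". The stated purpose is "to assess the prevalence of risk factors among apparently healthy infants and young children and assess the usefulness of the TRD case definition" in different settings. The Statistical analysis section describes how: "Analyses will be primarily descriptive, focused on substantive differences between cohorts, accompanied by visualisations and distribution-appropriate statistical testing". That sentence gives no alpha.

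The Sample size section powers the secondary question on risk factors across the community and the two hospital groups "under two-sided testing (of the null hypothesis that the adjusted OR is 1) with alpha=5" per cent. The Strengths and limitations box adds that, without a placebo group, the community cohort will serve as a cross-check on risk factors identified in hospital.

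**The concern.** A predictor counts as identified because it separates TRD from non-TRD children in the hospital data. Testing it again between those children partly repeats the selection step. A noise variable that happened to differ is more likely to be selected, and for the same reason more likely to give a small p-value. The TRD group's chance deviation also carries into TRD versus community, so that contrast is not a fully independent check of a selected predictor.

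The safeguards in the article do not reach this step. The variance inflation factor of 1.88 for variable selection applies to the primary AUROC sample size. Ten-fold cross-validation applies to AUROC estimation and to the choice of cut-off. The only inflation stated for the community cohort is 1.25, for blood collection failure.

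At stake is how the case definition is read. Small p-values printed beside selected predictors would look like corroboration when part of them comes from the selection itself.

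**Working it through.** **1. The plan's own power figure.** Inputs from Sample size: hospital split 60–106 versus 424–470, community 212, OR 1.6 per SD, covariates explaining 20% of the variable, two-sided 5%. Formula: power = Φ(√[N·p(1−p)·(1−R²)]·ln OR − 1.96).

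For 60 versus 212: N·p(1−p) = 60×212/272 = 46.76; times 0.8 = 37.41; square root 6.117; times ln 1.6 (0.470) = 2.875; minus 1.96 = 0.915; Φ = 82.0%. The other pairs give 94.2% (106 v 212), 86.6% (60 v 470) and 97.2% (106 v 424). The claim of at least 80% reproduces, as does 212×1.25 = 265. These calculations treat the tested variable as fixed in advance.

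**2. Simple bound on the selection effect.** If a null variable is kept when p<s and is then tested at 5% in the same data, P(p<0.05 | kept) = 0.05/s for s ≥ 0.05. The screening rules here are assumed: s = 0.05, 0.157 and 0.20 give 100%, 32% and 25%.

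**3. Elastic net, closer to the plan.** Assumptions: independent candidates, mixing parameter 0.5, penalty chosen by 10-fold cross-validation, linear-probability approximation, 120 runs per scenario, then a t-test in the same 530 children.

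| Candidates | Real predictors | TRD / non-TRD | Selected null with p<0.05, same children | Fresh children |
|---|---|---|---|---|
| 20 | 5 | 60 / 470 | 13.4% | 3.8% |
| 40 | 5 | 60 / 470 | 19.3% | 5.6% |
| 40 | 5 | 106 / 424 | 20.4% | 5.8% |
| 20 | 0 | 60 / 470 | 40.6% | 6.5% |
| 40 | 0 | 60 / 470 | 47.8% | 4.9% |

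A separate simulation (150 studies per scenario, 40 candidates, four real predictors with OR 1.6 per SD) gave 15–18% for TRD versus non-TRD and 13–16% for TRD versus community. With no real predictor it gave 47% and 35%. Null variables tested without selection gave 4.4–5.3%. Selection, not the test, causes the excess.

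**4. Which contrasts share the bias.** Under the null, the correlation between the TRD v non-TRD and TRD v community statistics is (1/n_T) / √[(1/n_T+1/n_N)(1/n_T+1/n_C)].
- 60/470/212: 0.01667 / (0.1371×0.1462) = 0.83.
- 106/424/212: 0.00943 / (0.1086×0.1190) = 0.73.

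For non-TRD v community the shared term is 1/n_N, and the absolute correlations are:
- 60/470/212: 0.00213 / (0.1371×0.0827) = 0.19.
- 106/424/212: 0.00236 / (0.1086×0.0841) = 0.26.

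A Monte Carlo run of the three statistics under the assumed screening rules (p<0.05, 0.157, 0.20) gave null rejection rates of 18–48% for TRD v community and about 6–9% for non-TRD v community.

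**5. Cut-off.** No calculation was made. The argument is structural: the final cut-off is chosen to separate the same two groups that are then compared on it.

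**The case against.** The strongest reply is that the plan already calls this comparison mainly descriptive, assigns validation of the model to cross-validated AUROC, and promises detailed analysis plans before analysis, where the choice of p-values could be settled. Much of that stands, and it lowers the stakes. It does not remove the point: the same sentence adds statistical testing, and the objectives fix both the variables compared and the children they are compared in.

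Four stronger readings are tempting but not supported.

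- A reader might infer that the plan commits to testing selected predictors at 5% and that this stated level fails. The 5% appears only in the power statement, for a generic risk factor.
- A reader might infer that TRD versus non-TRD is offered as confirmation. The objectives give prevalence and usefulness as the purpose, and the cross-checking role belongs to the community group.
- A reader might infer that selection adds false findings. In the 40-candidate simulation, 1.6–1.8 of about 5.5 significant predictors were false, but testing all 36 nulls without selection gives 36×0.05 = 1.8. The error rate among selected nulls rises; the count of false positives does not.
- A reader might take the rates of 41–48% as likely. They require that no candidate is real, although investigators are to choose plausible ones.

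The community contrast also needs care. Hospital children enter because they have at least one listed sign, so for those signs they differ from community children by design, and the null calculation says little. It matters more for dietary, maternal and other risk factors. For the cut-off, cross-validation does govern its choice, but the article does not extend it to the later cohort comparison.

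**Conclusion.** The point holds for a defined part of the plan. Naive p-values for TRD versus non-TRD on model-selected predictors are not valid at face value. TRD versus community is partly affected, and non-TRD versus community almost not at all. Under the assumed 20–40 candidates, cross-validated elastic net and four or five real predictors, the rate for a selected null predictor is roughly 13–20% for TRD versus non-TRD, against a nominal 5%. The article does not give the number of candidates, their correlation or the tuning rule, so this shows direction and plausible size and is not an estimate for this study. For the cut-off the same reasoning applies without a figure. Risk factors named in advance and not chosen by the model keep their per-test error rate, and the 80% power for an OR of 1.6 per SD is not disputed.

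**What to change.** In Objectives of study and Statistical analysis, state that TRD versus non-TRD contrasts of model-selected predictors and of the derived cut-off are reported as estimates without naive p-values. Alternatively, cross-fit them: select in the training folds and compare in the held-out fold, including for TRD versus community. In Sample size, state that the 5% alpha and the power apply only to risk factors specified before TRD status is linked to the data.

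The cost is wording and a little programming, with no change to enrolment or data collection. Some p-values will be less favourable or will not be reported.

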## Methods and analysis

### Study design and procedures

#### Study design

The study uses a prospective study design and includes a cohort of infants and young children 21 days to <18 months of age who are identified as having TDD-compatible symptoms (figure 1). Children will be recruited at the Lao Friends Hospital for Children (LFHC) in Luang Prabang, Lao PDR, and potentially eligible children presenting with any of the below described inclusion criteria will be identified through close collaboration between the LFHC hospital staff and the study team. Enrolled children will be treated with thiamine and all other clinically indicated treatments and followed closely over 48–72 hours, as described in more detail below. Based on the response to thiamine, children will either be defined as TRD cases or non-responders.

